### **Vital Signs**

All treatment visits have pre-dose vital sign assessments. Vital signs include: body temperature in degrees Celsius (°C), heart rate, blood pressure, and respiratory rate. On visit Day 1 only, minimum assessment frequency is every 15 min ( $\pm 5$  min) for 2 hours post dose; and assessment is taken every 30 min ( $\pm 5$  min) from 2 to 4 hours post dose. From 4 to 8 hours post-dose, measurements are taken every 60 min ( $\pm 10$  min). At the Day 2 Visit, vital signs will be assessed every 30 minutes ( $\pm 5$  min) for 2 hours post dose. Vital sign measurements are taken in a sitting position after at least 5 minutes of rest. Heart rate should be taken at each time point that blood pressure is measured. When blood samples and blood pressure assessments are scheduled at the same time or within the same time window, blood pressure should be measured before blood samples are drawn. Vital signs may be monitored more frequently or for longer duration post-dose as clinically indicated.

### **ECGs**

A standard 12-lead ECG will include heart rate, rhythm, intervals, axis, conduction defects, and anatomic abnormalities. If clinically significant abnormalities are noted, the Investigator or designee is required to assess whether it is appropriate for the subject to continue in the study. ECGs will be performed at the time points indicated in the Schedule of Activities (**Section 1.3**). All ECGs will be reviewed by a study investigator and if any questions arise, they will be reviewed by a cardiologist at Children's National Hospital.

### **Concomitant Medication Assessment**

A list of all medications will be assessed at the time points indicated in the Schedule of Activities (**Section 1.3**). The names of the medications will be recorded in a case report form. Dosing information will not be collected.

### **Echocardiogram**

Cardiac anatomy and function will be evaluated by a standard 2-dimensional Doppler ECHO. The data recorded is to include ventricular cavity size, valve characterization (presence or absence of valve stenosis or regurgitation and clinical significance), ventricular wall thickness, regional wall motion, LV mass calculation, and pericardial characterization. Echocardiograms will be performed at the time points indicated in the Schedule of Activities (**Section 1.3**).

### **Clinical Labs and Tissue Transglutaminase Antibody**

Clinical labs include: complete blood count with differential, complete metabolic panel, lipid panel, TSH, free T4, IGF-I, IGFBP-3, prolactin. All labs will be obtained through the clinical lab at Children's National Hospital which is a CLIA approved lab. Additionally, an extra 10 cc of blood will be obtained for storage for future analysis. This extra blood will be spun down for serum and plasma. The tubes will have the ID code as well as the date and time of collection recorded. These samples will be stored in [name] research laboratory at Children's National. Clinical labs will be performed at the time points indicated in the Schedule of Activities (**Section 1.3**). A Tissue Transglutaminase IgA antibody will be sent to the Children's National Hospital clinical lab at the Screening Visit as an assessment for celiac disease. Details of all laboratory specimen collections will be provided in the Laboratory Manual.

### **Anti-Vosoritide Immunogenicity Assessments**

Blood serum sampling for immunogenicity assessment will be performed at the time points indicated in the Schedule of Activities (**Section 1.3**). Total anti-BMN 111 immunogenicity analysis (TAb) and neutralizing antibodies (NAb) will be collected from serum. Samples will be collected prior to administration of vosoritide. TAb will be measured on all samples as indicated in the table. NAb will be stored and testing of NAb will only be triggered when a decline in cGMP signal is observed in the cGMP biomarker assay at both the 6 and 12 month visits in a TAb positive subject. Subjects with positive neutralizing antibodies will be monitored until the antibody levels return to baseline. Immunogenicity testing will be coordinated through BioMarin. Details of sample processing and shipping will be provided in the Lab Manual.

### **Bone Age and Spine X-rays**

Bone age and Spine X-rays will be performed using routine clinical protocols. The bone age X-rays will be done at an interval similar to routine clinical care. The spine X-ray will be a posteroanterior view of the spine. If the clinical examination suggests a new onset spine asymmetry, an additional spine X-ray will be performed at the 6 month visit. The radiation dose from a single spine X-ray is 1.5 mSv. For the inclusion criterion, the official clinical read of the bone age X-ray will be used to determine eligibility. At the conclusion of the study, all bone age X-rays will be read by a single centralized reader who is blinded to the age of the child and the time point that the X-ray was taken. The single reader will be either a radiologist or endocrinologist at Children's National. The images will only be labeled with the study ID. The ratio of bone age/chronological age will be calculated based on these values.

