Additional assessments noted in the prior paragraph will be repeated at the 6 and 12 month visits as detailed in the protocol. The dose of medication will be adjusted for weight at the 6 month visit if the subject has experienced weight changes.

During the extension phase, subjects will continue to be seen at Children's National every 6 months until growth cessation or subject withdrawal. Telephone visits will occur at the 3-month time point mid-way between each study visit.

**Study Duration:** 36 months; Extension phase of study may last up to an additional 15 years  
**Participant Duration:** 18 months; Extension phase may last up to ~15 years if a subject starts at age 3 years and stops growing at age 18 years

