## **EXTENSION PHASE DESIGN**

The extension phase will begin immediately after the 12-month visit. Eligible subjects will sign an addendum to the informed consent which outlines the details of participation in the extension study. Subjects will be seen in-person at Children's National every 6 months (+/- 2 weeks). Activities at the in-person study visits will include:

- Anthropometric Measurements
- Physical Exam
- Tanner Staging
- Vital Signs
- Quality of Life Survey
- Screening Labs
- Collagen X Marker sampling
- Vosoritide dose adjustment
- Review health events, concomitant medications, and medication administration
- Bone age X-ray – every 12 months
- DXA scan – every 24 months
- Additional safety imaging as needed due to clinical concern or prior abnormality

Additionally, subjects will have a telephone visit at the 3-month time point (+/- 2 weeks) between in-person visits. Activities at the telephone study visits will include:

- Review medication administration
- Review health events
- Assess for adverse events/concomitant medications

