#### 4.4 END OF STUDY DEFINITION

A participant is considered to have completed the study if he or she has completed all phases of the study including the last visit or the last scheduled procedure shown in the Schedule of Activities (SoA), Section 1.3.

The end of the study is defined as completion of the last visit or procedure shown in the SoA in the trial globally.

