#### 10.1.3 DATA CONFIDENTIALITY AND PARTICIPANT PRIVACY

Participant confidentiality and privacy is strictly held in trust by the participating investigators, their staff, and the sponsor(s) and their interventions. This confidentiality is extended to cover testing of biological samples and genetic tests in addition to the clinical information relating to participants. Therefore, the study protocol, documentation, data, and all other information generated will be held in strict confidence. No information concerning the study or the data will be released to any unauthorized third party without prior written approval of the sponsor/investigator and IRB.

All research activities will be conducted in as private a setting as possible, such as a clinic exam room.

The study monitor, other authorized representatives of the sponsor, representatives of the Institutional Review Board (IRB), regulatory agencies or BioMarin may inspect all documents and records required to be maintained by the investigator, including but not limited to, medical records (office, clinic, or hospital) and pharmacy records for the participants in this study. Children's National Hospital will permit access to such records.

The study participant's contact information will be securely stored at Children's National Hospital for internal use during the study. At the end of the study, all records will continue to be kept in a secure location for as long a period as dictated by the FDA, reviewing IRB, Institutional policies, or BioMarin requirements.

Study participant research data will be transmitted to and stored at BioMarin. This will not include the participant's contact or identifying information. Rather, individual participants and their research data will be identified by a unique study identification number. The study data entry and study management systems used by clinical site and by BioMarin will be secured and password protected.

Samples and data may be shared with collaborative laboratories/investigators for research purposes. Information pertaining to these procedures is included in the ICF and will be reviewed with participants during the consent process.

---

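### Bone-age films carry the participant's study ID, so the reader's time-point blind is weakly protected, and the date of the central read is ambiguous

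*Protocol*

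**What the plan says.** Under Bone Age and Spine X-rays, Section 8.2 of the Protocol sets out the central read. Its timing and reader are given as "At the conclusion of the study, all bone age X-rays will be read by a single centralized reader". This reader is to know neither the child's age nor the visit to which a film belongs. The label is then fixed: "The images will only be labeled with the study ID". The bone age/chronological age ratio is calculated from these readings. The reader is to be a radiologist or endocrinologist at the study hospital. The official clinical read is used only for eligibility.

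Section 10.1.3, on data passed to the manufacturer, says that participants and their data are "identified by a unique study identification number".

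The Schedule of Activities (Section 1.3) places bone-age films at Day 1 and Month 12. The extension adds "Bone age X-ray – every 12 months". Change in the ratio after 12 months is one of three secondary endpoints (Sections 1.1 and 3).

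On timing, Section 4.4 reads "The end of the study is defined as completion of the last visit or procedure shown in the SoA in the trial globally". Section 1.3 also contains the extension schedule. The synopsis gives a study duration of 36 months and then adds "Extension phase of study may last up to an additional 15 years".

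**The concern.** Section 3 gives the purpose of this endpoint: to show whether treatment advances bone age early and so limits remaining growth. The comparison is within child, Day 1 against Month 12, with no control arm. A reader who knows which of two films is later also knows which was taken on treatment. That reader may lean toward the yearly step he or she expects, or toward a larger one if drug-driven advance is expected. Either would distort the paired change, and the direction cannot be known in advance. Blinding to time point is the stated protection against this, and the stated label works against it.

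The second question is when the 12-month endpoint becomes available. Section 8.2 ties the reading to the end of the study without saying whether that means the initial part or the whole trial with its extension.

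**Working it through.** **1. Can one child's films be paired?** The label is the study ID (Section 8.2), and the ID is unique to the participant (Section 10.1.3). All films of one child therefore share a label. Section 8.2 states no per-image code and no random reading order. The label shows no age, date or visit.

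**2. How often would maturity reveal the order?** Let d be the bone-age advance over 12 months and s the reader's SD per film, with independent normal errors. The chance that the later film is read as the more mature is Φ(d / (s√2)). The Protocol gives neither d nor s, so both are assumptions.

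| d (years) | s = 0.25 | s = 0.5 | s = 0.8 |
|---|---|---|---|
| 0.7 | 0.976 | 0.839 | 0.732 |
| 1.0 | 0.998 | 0.921 | 0.812 |
| 1.3 | 1.000 (rounded) | 0.967 | 0.875 |

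For example, with d = 1.0 and s = 0.5: 1.0 / (0.5 × 1.414) = 1.414, and Φ(1.414) = 0.921. The order can usually be inferred, but not always.

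**3. How much could that move the endpoint?** Assume that knowing the order shifts the second reading by 0.25 year. The ratio then shifts by 0.25 / (age at Month 12).

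- Child aged 7 at Day 1 and 8 at Month 12: 0.25/8 = 0.031.
- Youngest: age 3 at screening, plus 6 months of observation and 12 of treatment, is about 4.5. 0.25/4.5 = 0.056.
- Oldest: a boy just under 11 at screening reaches about 12.5. 0.25/12.5 = 0.020.

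For scale, a child with ratio 1 at age 7 whose bone age truly advances 1.25 years in the year reaches 8.25/8 = 1.031. That change of 0.031 equals the assumed shift at the same age. The shift scales in proportion, so half the assumed shift gives half the effect.

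**4. How long could the 12-month readings wait?** The Protocol's figure of about 15 years for the extension reproduces as 18 − 3 = 15, but this counts from enrolment at age 3. Such a child is about 4.5 at Month 12, which leaves 18 − 4.5 = 13.5 years.

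- If the study ends as Section 4.4 defines it, with the extension schedule included, the reading could come up to about 13.5 years after that child's Month 12 visit. If that child closes the trial, films of children enrolled earlier wait longer by the gap in enrolment.
- If the study means the 36-month part, the first child can reach Month 12 at study month 6 + 12 = 18. The wait is at most 36 − 18 = 18 months, or 1.5 years.

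The 13.5 years is an upper figure. Sections 7.1 and 7.2 end extension participation on growth velocity or bone age, which may come before age 18.

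**The case against.** The best defence is that Section 8.2 states the requirement, a reader blinded to time point, and leaves file handling to operations. An imaging manual or SAP that is not shown may call for shuffling. The label hides age, date and visit, so blinding to age is untouched and order is only a guess from maturity. The endpoint is also one of three secondary endpoints in an exploratory study without power calculations.

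Most of that is fair, and it limits how far the point goes. It does not remove it. Section 8.2 is not silent on the label: it says the study ID and nothing else. A manual with per-image codes would contradict the Protocol, and random order alone would leave the shared ID visible.

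Some stronger readings are tempting but not supported:

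- **That the blind cannot hold.** Order is inferred, with the probabilities above resting on assumed inputs.
- **That late reading breaks the blind.** It does not. One late batch is what allows visits to be mixed; the weakness is the shared ID.
- **That the number of films under an ID identifies responders.** Extra yearly films point that way, since the extension requires a positive response. But Section 5.1 admits some children below the 3 cm/year threshold after a poor response to growth hormone, and responders may decline or be excluded on bone age. The clue exists only if extension films are in view in the same batch.
- **That the endpoint must wait for the extension.** The synopsis lists 36 months separately, and Section 6.2.1 speaks of the entire study when it means the final end. Section 4.4 supports the longer wait, but Section 8.2 does not choose.
- **That the 12-month report must fall back on clinical reads or drop the endpoint.** The Protocol provides for neither.

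**Conclusion.** The point stands in a limited form, as two separate defects of wording.

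First, the label chosen in Section 8.2 undercuts the time-point blind that the same section promises. One child's films can be paired, and their order, off treatment against on treatment, can often be inferred. The blind is weakly protected rather than lost. The possible effect on the ratio is about 0.031 at age 8, with 0.020 to 0.056 across eligible Month 12 ages. This rests wholly on an assumed shift of 0.25 year, and its direction is unknown.

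Second, the timing of the reading is open to two interpretations that differ widely: at most about 1.5 years, or up to about 13.5 years after a child's Month 12 visit.

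The primary endpoints and eligibility do not depend on the central read. The correction is worth making because this endpoint is the Protocol's check on early bone-age advance and the remedy is cheap.

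**What to change.** Amend the bone-age text of Section 8.2 as follows.

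1. Replace the study-ID label with a unique random code for each image, unrelated to the study ID, with the key held by a data manager.
2. Have the same reader score films singly, in random order across children and visits.
3. State that all Day 1 and Month 12 films are read in one batch after the last child's Month 12 visit.
4. Read extension films in later batches, each including some re-coded earlier films so that drift between batches can be measured.

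The cost is the relabelling work and a few changed sentences. No new X-rays and no second reader are needed. The small downside is that the reader works in more than one batch, which the re-coded films are there to monitor.

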### **Adverse Events**

The occurrence of AEs will be assessed continuously from the time the subject signs the ICF. The determination, evaluation and reporting of AEs will be performed as outlined in Section 8.3. Assessments of AEs will occur at the time points shown in the Schedule of Activities (Section 1.3).

NOTE: These safety assessments (except for X-rays) may be done at additional time points at the discretion of the PI in order to monitor for the development of adverse events or to ensure that the subject's baseline status has not changed which would preclude participation. X-rays are excluded as they increase the radiation exposure. For example, extra echocardiograms may be ordered if recommended by the study cardiologist.

### **Safety Imaging During the Extension Phase**

The extension phase of the study may last many years as subjects enrolled at age 3 years could have up to 15 years until growth cessation. We will conduct yearly bone age and DXA assessments every 2 years as part of the follow up evaluation. However, we will not do additional routine imaging in order to avoid excessive radiation exposure. If there is concern for a musculoskeletal issue (e.g. worsening scoliosis, bone pain or deformity), additional imaging will be ordered by the investigator as clinically appropriate to assess the concern. Additionally, routine follow up echocardiograms will not be performed after the 12 Month Visit. However, if the study cardiologist has any concerns based on the echocardiogram done at the 12 Month Visit, she may recommend additional echocardiograms at her discretion.

## **8.3 ADVERSE EVENTS AND SERIOUS ADVERSE EVENTS**

### **8.3.1 DEFINITION OF ADVERSE EVENTS (AE)**

Adverse event means any untoward medical occurrence associated with the use of an intervention in humans, whether or not considered intervention-related (21 CFR 312.32 (a)).

For this protocol, a reportable AE is any untoward medical occurrence (eg, sign, symptom, illness, disease or injury) in a subject administered the study-drug or other protocol-imposed intervention, regardless of attribution. This includes the following:

- AEs not previously observed in the subject that emerge during the course of the study.
- Pre-existing medical conditions judged by the Investigator to have worsened in severity or frequency or changed in character during the study.
- Complications that occur as a result of non-drug protocol-imposed interventions (e.g., AEs related to screening procedures, medication washout, or no-treatment run-in).
- Clinically significant post-screening test results that require medical intervention.

An adverse drug reaction is any AE for which there is a reasonable possibility that the study drug caused the AE. "Reasonable possibility" means there is evidence to suggest a causal relationship between the study-drug and the AE.

After informed consent but prior to initiation of vosoritide, only SAEs associated with any protocol-imposed interventions will be reported.

---

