#### **Endpoints:**

The primary study endpoints include:

- Incidence of adverse events per subject with particular attention to Grade 3 and 4 adverse events as well as to rates of hypotension
- Change from baseline in age-sex standardized annualized growth velocity after 12 months of treatment
- Change from baseline in age-sex standardized height SDS after 12 months of treatment

The secondary study endpoints include:

- Change from baseline in seated height ratio after 12 months of treatment
- Change from baseline in arm span minus standing height after 12 months of treatment
- Change from baseline in bone age/chronological age after 12 months of treatment

During the extension study, all of the endpoints will remain the same, but the timeframe will be extended from 12 months until growth cessation or subject withdrawal from the study.

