b All treatment visits have pre-dose vital sign assessments. Vital signs include: body temperature in degrees Celsius (°C), heart rate, BP, and respiratory rate. On visit Day 1 only, minimum assessment frequency is every 15 min ( $\pm 5$  min) for 2 hours post dose; and assessment is taken every 30 min ( $\pm 5$  min) from 2 to 4 hours post dose. From 4 to 8 hours post-dose, measurements are taken every 60 min ( $\pm 10$  min). At the Day 2 Visit, vital signs will be assessed every 30 minutes ( $\pm 5$  min) for 2 hours post dose. Vital sign measurements are taken in a sitting position after at least 5 minutes of rest. Heart rate should be taken at each timepoint that BP is measured. When blood samples and BP assessments are scheduled at the same time or within the same time window, BP should be measured before blood samples are drawn. Vital signs may be monitored more frequently or for longer duration post-dose as clinically indicated.

c Anthropometric measurements include standing height, weight, sitting height, head circumference and arm span. Standing height should be measured 5 times using a calibrated stadiometer. Sitting height should be measured three times. Weight should be measured on a digital scale.

d Clinical labs include: complete blood count with differential, complete metabolic panel, lipid panel, TSH, free T4, IGF-I, IGFBP-3, prolactin. All labs will be obtained through the clinical lab at Children's National Hospital. Additionally, an extra 10 cc of blood will be obtained for storage for future analysis.

e Antibodies: Total anti-BMN 111 immunogenicity analysis (TAb) and neutralizing antibodies (NAb) will be collected from serum. TAb will be measured on all samples as indicated in the table. NAb will be stored and testing of NAb will only be triggered when a decline in cGMP signal is observed in the cGMP biomarker assay at both the 6 and 12 month visits in a TAb positive subject.

f PK: On Day 1 and months 6 and 12, PK plasma samples are collected pre-dose and at 5 ( $\pm 2$  min), 15 ( $\pm 2$  min), 30 ( $\pm 5$  min), 60 ( $\pm 5$  min), 90 ( $\pm 5$  min), 120 ( $\pm 5$  min), and 180 ( $\pm 5$  min) min post-dose.

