#### 8.3.4 TIME PERIOD AND FREQUENCY FOR EVENT ASSESSMENT AND FOLLOW-UP

The occurrence of an adverse event (AE) or serious adverse event (SAE) may come to the attention of study personnel during study visits or phone contacts with a study participant. Assessments for AE will occur as outlined in the Schedule of Activities (**Section 1.3**).

All AEs including local and systemic reactions not meeting the criteria for SAEs will be captured on the appropriate case report form (CRF). Information to be collected includes event description, time of onset, clinician's assessment of severity, relationship to study product (assessed only by those with the training and authority to make a diagnosis), and time of resolution/stabilization of the event. All AEs occurring while on study must be documented appropriately regardless of relationship. All AEs will be

followed until the event has resolved or any permanent sequelae are stable. The study team will work with the local clinicians to determine the characterization and severity of an AE and the proper course of treatment, if appropriate.

Any medical condition that is present at the time that the participant is screened will be considered as baseline and not reported as an AE. However, if the study participant's condition deteriorates at any time during the study, it will be recorded as an AE.

Changes in the severity of an AE will be documented to allow an assessment of the duration of the event at each level of severity to be performed. AEs characterized as intermittent require documentation of onset and duration of each episode.

The study coordinator, with supervision of the PI, will record all reportable events with start dates occurring any time after informed consent is obtained until 7 (for non-serious AEs) or 30 days (for SAEs) after the last day of study participation. At each study visit, the investigator will inquire about the occurrence of AE/SAEs since the last visit. Events will be followed for outcome information until resolution or stabilization. For events that are not resolved or stable at the last study visit, the study team will continue to contact the family by phone on a weekly basis until resolution or stabilization.

---

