### 9.1 STATISTICAL HYPOTHESES

- Primary Safety Endpoint(s): We will rule out safety concerns. That is, we will rule out the null hypothesis that risk of adverse events post-drug administration will be more than twice the risk during the baseline period (i.e, RR or OR > 2).
- Primary Efficacy Endpoint(s): The null hypothesis is that there is no change from baseline in annualized growth velocity or height SDS over the 12 months of intervention when compared to the 6 month baseline observation period. The alternate hypothesis is that there is a change from baseline in these values.
- Secondary Efficacy Endpoint(s): The null hypothesis is that there is no change from baseline in seated height ratio, arm span minus standing height, or bone age divided by chronological age over the 12 months of intervention when compared to the 6 month baseline observation period. The alternate hypothesis is that there is a change from baseline in these values.

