### 9.4 STATISTICAL ANALYSES

#### 9.4.1 GENERAL APPROACH

Analyses on all endpoints will be self-controlled, comparing measurements for each subject during follow-up to the same measurements during the baseline period. Thus, all measurements will be summarized for baseline period (control period), and during follow-up (test drug period). Descriptive statistics will be presented for all measures of change from baseline (mean, standard deviation, median, interquartile range, min and max). Comparisons between baseline period and follow-up period will use a paired t-test for continuous endpoints and a chi-square test for dichotomous endpoints. If there are departures from normality or small samples, we will use Mann-Whitney test for comparison of medians and exact Clopper-Pearson test for comparison of dichotomous endpoints.

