#### 9.4.5 BASELINE DESCRIPTIVE STATISTICS

Descriptive statistics of the cohort will be based on the 6 month observation period. These will include baseline height velocity, height SDS, body proportions, quality of life score, and adverse events. They will be described as noted in Section 9.4.1 above.

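### Section 8.3.1 limits pre-treatment reporting to procedure-related SAEs, contradicting the sections that collect all AEs from consent and leaving the control data for the primary safety comparison undefined

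*Protocol*

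**What the plan says.** The primary safety endpoint (Protocol 1.1 and Section 3) is "Incidence of adverse events per subject with particular attention to Grade 3 and 4 adverse events as well as to rates of hypotension". Section 9.1 seeks to rule out the null hypothesis that "risk of adverse events post-drug administration will be more than twice the risk during the baseline period", given as RR or OR above 2. Section 9.4.1 fixes the control: "Analyses on all endpoints will be self-controlled, comparing measurements for each subject during follow-up to the same measurements during the baseline period". Section 9.4.5 lists the baseline descriptive statistics: "These will include baseline height velocity, height SDS, body proportions, quality of life score, and adverse events".

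On collection before dosing, the protocol gives two rules.

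- Restrictive. The last sentence of 8.3.1: "After informed consent but prior to initiation of vosoritide, only SAEs associated with any protocol-imposed interventions will be reported".
- Inclusive. Section 8.2 (Adverse Events): "The occurrence of AEs will be assessed continuously from the time the subject signs the ICF". Under 8.3.4 the study coordinator "will record all reportable events with start dates occurring any time after informed consent is obtained", in a window that covers non-serious as well as serious AEs. Section 8.3.4 also requires non-serious AEs to be captured on the CRF, and on-study AEs to be documented whatever their relationship to drug. The Schedule of Activities (1.3) marks AE review at screening and at each monthly baseline call.

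On monitoring intensity, footnote b of the Schedule of Activities says "On visit Day 1 only, minimum assessment frequency is every 15 min" for the first two hours after the dose. Less frequent readings follow to 8 hours, and there is a further 2-hour series on Day 2. The observation period has no comparable series.

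**The concern.** The comparison in 9.1 is only as good as the count in its control period. If one rule governs before dosing and another after it, ordinary childhood illness is left out of the first period and counted in the second. The ratio then measures the recording rule as well as the drug.

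This touches a primary endpoint, and an analysis plan cannot repair it, because it concerns which data are captured. Baseline events not recorded at the time become harder to recover. Two site staff could follow different sentences and both be compliant.

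How closely children are watched also changes at Day 1. This matters most for hypotension, which the endpoint names and which is found largely by measuring blood pressure.

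**Working it through.** The protocol gives no safety sample size, alpha, power or expected AE rate, so it has no figure of its own to reproduce. The only number is the margin of 2.

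**1. Which rule governs?** Section 8.2 assesses AEs from consent, but then refers determination, evaluation and reporting to 8.3, where the restriction sits. Section 8.3.4 opens its window at consent, but for reportable events, a term defined in 8.3.1. That definition covers illness regardless of attribution and lists complications of a no-treatment run-in. Its closing sentence then narrows the pre-dose period to procedure-related SAEs. Each route leads back to 8.3.1, which disagrees with itself.

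**2. Effect of under-recording.** Assume a constant AE rate and no drug effect. Let f be the share of baseline AEs recorded and d the relative detection on drug.

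Observed rate ratio = d / f

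| f (assumed) | Rate ratio, d = 1 |
|---|---|
| 1.00 | 1.00 |
| 0.75 | 1.33 |
| 0.50 | 2.00 |
| 0.25 | 4.00 |
| 0.10 | 10.0 |

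The margin of 2 is reached at f = d / 2: 0.50 if d = 1, 0.625 if d = 1.25, and 0.75 if d = 1.5 (d assumed). If only procedure-related SAEs were kept, f would be near 0 and the ratio uninterpretable.

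**3. AE-review contacts (1.2 and 1.3), taking bi-weekly as every two weeks (assumption).**

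- Baseline: screening + 5 monthly calls = 6 in 6 months, 1.0 per month. Counting the pre-dose part of Day 1 as well gives 7, or 1.17 per month.
- Drug months 0-6: Day 1 + Day 2 + 3 daily calls + about 10 bi-weekly calls + 6-month visit = 16, or 16/6 = 2.67 per month.
- Drug months 7-12: 5 monthly calls + 12-month visit = 6, or 1.0 per month.
- Whole drug period: 22/12 = 1.83 per month.

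Contact density relative to baseline is 16/7 to 16/6 = 2.3 to 2.7 times in the first half, about equal in the second, and 1.83/1.17 to 1.83/1.0 = 1.6 to 1.8 times overall.

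**4. Scheduled blood pressure readings (footnote b).** Post-dose Day 1: 120/15 + 120/30 + 240/60 = 8 + 4 + 4 = 16. Post-dose Day 2: 120/30 = 4. Total 20. Untreated readings: one at screening and one pre-dose on Day 1 = 2.

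**5. Does complete baseline recording suffice?** Not for a per-subject risk, because the periods are 12 and 6 months. With 6-month risk p, a constant rate and no drug effect, the 12-month risk is 1 − (1 − p)². Hence RR = 2 − p and OR = (2 − p)/(1 − p).

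| p (assumed) | RR | OR |
|---|---|---|
| 0.10 | 1.90 | 2.11 |
| 0.30 | 1.70 | 2.43 |
| 0.50 | 1.50 | 3.00 |
| 0.80 | 1.20 | 6.00 |

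Unequal follow-up alone puts the OR above 2 across this range. With rates per person-time, f = 1 and d = 1, the ratio is 1.00.

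**The case against.** The strongest defence is that the protocol plainly intends to collect baseline AEs. The capture and documentation requirements in 8.3.4 are broad, AE review is scheduled at every baseline call, and 8.2 gives families a Health Events Diary. The amendment history says the monthly baseline calls were added to assess safety in that period. On this view, reported in 8.3.1 means onward reporting to outside parties. That is plausible and may be what the site does, but the protocol nowhere says it, and 8.3.4 ties recording to reportability. The contradiction stands; the intent lowers the likelihood of the worst case.

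A reader might infer that the drug period is bound to look worse, or that the trial has no valid control. The documents do not support either. Both need the 8.3.1 sentence to override every inclusive passage, and the protocol gives no AE counts from which a particular inflated ratio could be derived. A reader might also infer that harm could be hidden. Missing baseline events work the other way: they raise the ratio and make RR above 2 harder to rule out.

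On surveillance, more contacts do not convert proportionally into more AEs, since 8.3.4 asks at each visit about events since the last one. The contact excess is confined to the first six drug months. Close first-dose observation is a safety measure and is not criticised here.

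Section 9.4.4 calls the end-of-study safety analysis descriptive, and 9.1 attaches no separate margin to hypotension. Both are true, but a descriptive self-controlled comparison needs the same baseline data. The handling of exposure time and post-dose readings may be settled in an SAP that is not at hand; what is recorded at baseline is a protocol matter.

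**Conclusion.** The point holds as an internal contradiction. The last sentence of 8.3.1 cannot be reconciled with 8.2, 8.3.4, 9.4.5 and the Schedule of Activities, and it undercuts the comparison in 9.1. The size of the bias depends on the rule the site followed. Complete recording leaves none from this source; half recorded gives a rate ratio of 2 with no drug effect and equal detection; literal use of 8.3.1 leaves nothing usable as a control. These figures rest on a constant AE rate and on assumed values of f and d.

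Two lesser problems remain once the sentence is corrected. Contacts are denser in the first six drug months, and post-dose blood pressure is read 20 times on Days 1-2 against about 2 untreated readings. The 12 versus 6 months of follow-up also distorts any unadjusted RR or OR.

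**What to change.** 1. Reword the end of 8.3.1: from consent, all AEs, serious or not and related or not, are recorded on the AE form; any limit before the first dose applies only to expedited or onward reporting. Align 8.2 and 8.3.4 with this rule.
2. For children already past baseline, enter events documented at the monthly calls and in the Health Events Diary, each flagged as a retrospective entry.
3. Express the 9.1 contrast as exposure-adjusted AE rates, or confirm that the SAP does so.
4. Add a sensitivity comparison of drug months 7-12 with baseline, where contact density is about equal.
5. Restrict the between-period hypotension comparison to symptomatic events and pre-dose visit readings. Report post-dose readings separately.

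The monitoring schedule itself need not change. The cost is a wording amendment, a CRF instruction and some back-entry. The downside is possible recall or open-label bias in the retrospective entries, which is why they should be flagged so that results can be shown with and without them.
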